##### Sequential trials design

In the sequential trials design, the sequence of emulated ‘trials’ will be constructed and then pooled (ie, stacked) together for the analysis. Adjusted Cox proportional hazards regression models will be used to estimate conditional HRs, including treatment status at the start of each trial and adjusting for the baseline confounders in each trial.

Conditional HRs (adjusted for baseline covariates) from a cause-specific model for pulmonary exacerbation will be presented. We will also obtain estimates of marginal cumulative incidences based on the cause-specific hazard models for pulmonary exacerbation, and for the competing events of death and transplant, followed by empirical standardisation. Marginal risk differences at 6 months will be obtained from the marginal cumulative incidences. Bootstrapping will be used when estimating all 95% CIs.^38^

As in the PNUD, in addition to the ITT estimate, the PP effect will be estimated by censoring individuals when they deviate from their assigned treatment strategy within each artificial trial. IPCW weights will be derived as specified in the PNUD above, but separately in each artificial trial.

See online supplemental material appendix 1 for additional information on estimands, data analysis and analysis of secondary outcomes.

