Treatment strategies	Following a 2-month run-in period receiving fluticasone propionate, participants either: continue to take fluticasone, or switch to taking placebo.	Participants either: continue to take ICS (any ICS, not limited to fluticasone propionate) for the duration of follow-up, or discontinue ICS and remain not taking it for the duration of follow-up.	Prevalent new-user design: Same as target trial, with information on (dis)continuation obtained using prescription start and stop dates. Sequential trials design: Same as the PNUD.
Assignment procedures	Randomisation to treatment strategy Investigators and participants blinded to assignment.	Same as CF-WISE.	Prevalent new-user design: For each discontinuer, comparators will be selected into time-based exposure sets that correspond to each ICS discontinuer. Comparators within each exposure set will then be reweighted to resemble the discontinuers. Sequential trials design: Sequence of artificial ‘trials’, with discontinuers and continuers defined within each regularly spaced ‘trial’. Potential for re-use of continuers across multiple trials. Confounder adjustment is through regression. In the absence of randomisation, treatment assignment is assumed to be random conditional on ICS treatment history and the measured covariates specified in *Covariates*.
Follow-up and index date	Follow-up starts at randomisation and ends at loss to follow-up, meeting criteria for early trial withdrawal, or 6 months of follow-up, whichever occurs first.	Same as CF-WISE	Prevalent new-user design: Follow-up starts at date of ICS discontinuation for both the discontinuers and the reweighted continuers. Sequential trials design: Follow-up starts at the date of ICS discontinuation for the discontinuers and the date of the start of each successive ‘trial’ for the continuers in that trial. For the primary outcome, individuals will be followed up to first pulmonary exacerbation, death, transplant or 6 months after treatment assignment, whichever occurs first. For information on follow-up for secondary outcomes (lung function) see online supplemental material appendix 1.

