### Data analysis

#### Causal estimands

Causal estimands are a way to clearly describe the target of treatment effect estimation.^31^ In an RCT, the average treatment effect in the treated (ATT) and an alternative estimand, the average treatment effect in the whole population (ATE), are the same due to randomised treatment assignment.^24^ In observational data, however, the ATT and the ATE differ because the characteristics of the treated subgroup differ from those of the whole eligible population. In our study, the ATT targets the question: ‘how would the outcomes in those discontinuing ICS have differed, on average, had they continued on ICS?’. By contrast, under the ATE, we ask the question: ‘how would the outcomes in the population differ, on average, had everyone discontinued ICS versus continued on ICS?’.^24^

The PNUD specifically targets an ATT, whereas the sequential trials design, which makes use of all continuers in the study (figure 4) can be used to estimate an ATE or ATT through different analysis steps. This work will establish which estimands are targeted in both study designs, interpret any differences between them and explore how data obtained under the sequential trials design can be used to target the ATT as well as an ATE, and hence allow valid comparison between results obtained under the two designs.

HRs for time to pulmonary exacerbation associated with ICS discontinuation will be the primary causal estimand of interest. HRs are assumed to be constant over time and will allow for empirical benchmarking of the findings to the CF-WISE trial. The marginal risk difference will also be estimated to compare the risk of pulmonary exacerbation associated with discontinuation up to a time horizon of 6 months following treatment assignment.

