#### Main analysis

##### Prevalent new-user design

In the PNUD, continuers within each exposure set will be weighted to resemble the discontinuers using propensity score (PS) weighting methods described elsewhere as time-stratified standardised morbidity ratio weighting.^32^,^34^ We will fit a logistic regression model across all exposure sets with treatment discontinuation as the outcome, adjusting for time and the covariates specified in *Covariates*, to estimate the probability of discontinuing versus continuing ICS, deriving weights as follows: discontinuers will receive a weight of 1, and continuers will be weighted by their odds of discontinuing (ie, where PS denotes an individual’s probability of being a discontinuer conditional on their covariate set, and continuers are weighted as PS/(1−PS)).^35^

A weighted Cox proportional hazards model, including treatment status (discontinue versus continue) as the only covariate, will be used to estimate HRs for time to first pulmonary exacerbation, along with bootstrapping used to obtain corresponding 95% CIs. Individuals are censored at the time of death or transplant in this analysis. Marginal cumulative incidence curves will also be estimated under the two treatment strategies. This will be achieved by applying a weighted Aalen-Johansen estimator separately in the discontinuers and the continuers. The analysis takes account of the competing events of death or lung transplant.^36^

The above approach gives an estimate of the ITT effect. Estimation of the PP effect will involve censoring individuals who deviate from their baseline treatment status, which will be accounted for using inverse probability of censoring weighting (IPCW). The probability of remaining uncensored up to a given time will be estimated based on a Cox regression where censoring is the outcome and adjustment is made for the baseline covariates (the same covariates adjusted for in the PS-based weighting procedure). These probabilities will be used to derive IPCW weights to be used in the analysis (weighted Cox proportional hazards model and weighted Aalen-Johansen estimator).^37^

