#### Comparison of methods

The PNUD and sequential trials design were recently compared under the target trial framework and questions remain around the estimands they target, their suitability to discontinuation questions and model precision in smaller samples.^20^ In addition to benchmarking with CF-WISE, we will compare the point estimates and 95% CIs obtained under both designs. Discussion and exploration of comparisons between the two study designs will also be undertaken, namely with respect to causal estimands, eligibility and cohort definitions, interpretability and computational efficiency.

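### On the primary hazard-ratio scale, the between-design comparison sets a marginal ATT hazard ratio (PNUD) against a covariate-conditional one (sequential trials), and moving from ATE to ATT does not align them

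*Protocol article*

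**What the plan says.** **Primary scale.** Under Causal estimands: "HRs for time to pulmonary exacerbation associated with ICS discontinuation will be the primary causal estimand of interest". The HR is taken to be constant over time, and a marginal risk difference at 6 months is also estimated.

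**PNUD.** Causal estimands states: "The PNUD specifically targets an ATT". Under Main analysis, "discontinuers will receive a weight of 1, and continuers will be weighted by their odds of discontinuing". The weighted Cox model is then described as "including treatment status (discontinue versus continue) as the only covariate, will be used to estimate HRs for time to first pulmonary exacerbation". That gives a marginal HR in the discontinuers.

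**Sequential trials.** Under Main analysis: "Adjusted Cox proportional hazards regression models will be used to estimate conditional HRs". The HR to be presented is this conditional one, from a cause-specific model. Standardisation is planned for cumulative incidences and the 6-month risk difference. No marginal HR is named.

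**Comparison.** Under Comparison of methods: "we will compare the point estimates and 95% CIs obtained under both designs". Causal estimands adds that the work will establish which estimands the designs target and explore an ATT as well as an ATE from the sequential data, so that the comparison is valid.

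**ICS history.** Table 1 (Assignment procedures) says "treatment assignment is assumed to be random conditional on ICS treatment history and the measured covariates". The list under Covariates does not name ICS duration or history. The Variables section makes specifications common to both designs, and the sequential model is said to adjust for the baseline confounders.

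**The concern.** The second objective is to compare the designs and interpret any differences. On the primary scale, the visible plan would compare a marginal HR with a conditional one. The safeguard it offers, ATT versus ATE, concerns whose effect is averaged. It does not concern whether the HR is conditional on covariates.

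The sequential model as described contains treatment and confounders, with no treatment-by-covariate interactions named. Such a model returns a single conditional HR, which has no separate ATT and ATE versions. The planned ATT work can therefore change the standardised risks, but no stated step changes the HR.

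A reader could take a gap between the two HRs as evidence about the designs when part of it is only a difference of scale. The constant-HR assumption has a related weakness. Away from the null, a constant conditional HR generally implies a marginal HR that varies over time, so the assumption cannot generally hold exactly in both models.

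**Working it through.** **No planned figure to reproduce.** The article gives no event count, power or expected between-design difference. Its one effect estimate is the index-trial HR of 1.07 (0.68 to 1.70). That interval is coherent: √(0.68 × 1.70) = 1.075, and the SE of log HR is ln(1.70/0.68)/(2 × 1.96) = 0.234. It is reported for fluticasone versus placebo; inverted, it runs from 1/1.70 = 0.59 to 1/0.68 = 1.47. I use it only for plausible effect sizes.

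**Inputs from the article:** 6 months of follow-up; 536 discontinuers before the other exclusions.

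**Assumptions not in the article:** SD σ of the covariate linear predictor 0.5 to 1.5; 6-month risk r among continuers 15% to 50%; perfect covariate balance; no effect modification; equal arm weight.

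**Method.** Let the hazard be λ·exp(bA + σZ), with Z standard normal and independent of treatment A. The conditional HR is exp(b). Arm-specific survival is S_a(t) = E_Z[exp(−λt·exp(ba + σZ))], with λ chosen so that 1 − S_0(6 months) = r. The marginal HR exp(β) solves the treatment-only Cox score equation, with p(t) = S_1·exp(β)/(S_1·exp(β) + S_0):

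Σ_t {½dF_1 − (½dF_1 + ½dF_0)·p(t)} = 0

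**Marginal HR implied by each conditional HR:**

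| Conditional HR | r = 15%, σ = 0.5 | r = 30%, σ = 1.0 | r = 50%, σ = 1.5 |
|---|---|---|---|
| 1.00 | 1.000 | 1.000 | 1.000 |
| 1.07 | 1.068 | 1.058 | 1.043 |
| 1.30 | 1.292 | 1.243 | 1.175 |
| 1.50 | 1.484 | 1.396 | 1.281 |
| 1.70 | 1.676 | 1.543 | 1.380 |
| 0.68 | 0.685 | 0.719 | 0.782 |

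The outer columns are the extremes over the grid (r = 15%, 30%, 50%; σ = 0.5, 1.0, 1.5).

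**Against sampling error.** SE(log HR) ≈ √(1/E + 1/(sE)), with E = 536r events among discontinuers and s = 1 to 4 effective continuers per discontinuer (assumed).

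- r = 15%: E = 80.4, SE 0.125 to 0.158
- r = 30%: E = 160.8, SE 0.088 to 0.112
- r = 50%: E = 268, SE 0.068 to 0.086

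At 1.07 the largest gap is ln(1.07/1.043) = 0.026, well under one SE. At 1.50 in the middle scenario it is ln(1.50/1.396) = 0.072, or 0.6 to 0.8 SE. At 1.50 in the extreme scenario it is ln(1.50/1.281) = 0.158, or 1.8 to 2.3 SE.

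**Precision of the between-design difference.** Both estimates draw on the same registry people, so they are correlated. With illustrative SEs of 0.10 each and correlation ρ, the SE of the difference is 0.10·√(2(1 − ρ)): 0.077 at ρ = 0.7, 0.045 at ρ = 0.9, and 0.141 if independence were assumed.

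**ICS history, a separate matter of confounding.** For a binary history variable with outcome HR g and prevalence p1 in discontinuers and p0 in continuers, the approximate bias factor from omitting it is (1 + p1(g − 1))/(1 + p0(g − 1)). With g = 1.5, p1 = 0.4 and p0 = 0.6 (all assumed), this is 1.2/1.3 = 0.92.

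**The case against.** The strongest reply is that differing estimands are the declared subject of the study. The objectives, Causal estimands and Comparison of methods all promise to establish, compare and discuss them, and the sequential HR is openly labelled conditional. A common marginal scale also exists: both designs yield a 6-month risk difference, and the comparison is not restricted to HRs. Appendix 1, which covers estimands and analysis, is not shown.

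Much of this stands. Once both designs target the discontinuers, the risk difference is free of the problem. What it does not answer is that the HR is the primary estimand, the risk difference is not named as the measure for comparing designs, and the only alignment described is ATT versus ATE.

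Three stronger readings are tempting but unsupported:

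- That the two HRs must differ even if both designs are unbiased. Without effect modification they coincide at 1 and are nearly equal at 1.07.
- That the sequential analysis omits ICS history, and that this is part of the same problem. Omission is only an inference from the covariate list; Table 1 names history as a conditioning variable, and appendix 1 may settle it. If history confounds and is left out, the result is bias, not non-collapsibility.
- That comparing two separate CIs is an underpowered test. The article states no overlap test, independence assumption or decision rule, and nothing in it rules out a paired bootstrap.

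**Conclusion.** The point holds in limited form. On the primary scale the visible plan compares a marginal ATT HR with a covariate-conditional HR, and re-targeting the sequential design to the ATT does not by itself bring them together.

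The consequence depends on the effect size. It is nil at the null and negligible near the index-trial estimate. It can be material for larger effects: a conditional HR of 1.30 corresponds to a marginal 1.18 to 1.29, 1.50 to 1.28 to 1.48, and 1.70 to 1.38 to 1.68. These ranges rest on the assumed covariate spread and risk, with no effect modification.

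ICS history is a separate inconsistency in the text, to be reconciled as a possible confounding issue. The joint bootstrap is an inexpensive improvement, not the correction of an error.

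**What to change.** 1. For the between-design comparison, also fit in the stacked sequential data a Cox model with treatment only and propensity-odds weights (1 for discontinuers, PS/(1 − PS) for continuers). Standardise the 6-month risks over the discontinuers.
2. Name this marginal ATT HR and the ATT risk difference as the measures compared with the PNUD. Keep the conditional HR as secondary. With both designs on one scale and one target population, the non-collapsibility gap is removed by construction.
3. As an addition, resample individuals once, run both designs in each bootstrap sample, and report a CI for the between-design difference in log HR and in risk difference.
4. Separately, reconcile Table 1 with Covariates and the sequential model by including time since ICS start in that model, or point to appendix 1 if it already does so.

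The cost is one extra weighted model, one more covariate and a shared resampling scheme. Both designs already use bootstrapping, so run time rises modestly and no new data item beyond the recorded ICS dates is needed.

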#### Sequential trials design

The sequential trials design is an alternative method which has elsewhere been referred to as the sequential trials approach, successive trials or sequential Cox approach.^20^,^22^ Under this design, a sequence of artificial ‘trials’ will commence at successive regularly spaced time points. At each time origin, the set of individuals meeting the eligibility criteria will be divided into ICS discontinuers and continuers based on treatment start and stop dates as recorded in the UKCFR, emulating a series of successive ‘trials’ from January 2016 to June 2018 (see figure 3). For example, this may entail successive monthly trials within which continuers and new discontinuers are identified. Eligible individuals who continue ICS may be included in multiple artificial trials. For example, individuals eligible for the trial commencing January 2016 but who do not discontinue ICS in that period will be eligible to be included in the next trial if they meet the eligibility criteria, and so on. Eligible individuals can appear as discontinuers in only one trial, but discontinuers may appear in earlier trials as continuers.

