##### Sequential trials design

The same study period between 1 January 2016 and 30 June 2018 is specified, organised into regularly spaced (eg, monthly) artificial trials within that time period. Individuals are eligible for the first trial if they meet all the eligibility criteria (see *Inclusion and exclusion criteria*) on 1 January 2016. This approach is then applied, with updated covariate data where available (at annual reviews), to every successive new time origin between January 2016 and June 2018.

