## Data checks and feasibility analysis

Preliminary inspection of the UKCFR data to address feasibility queries was undertaken. The main objective was to ascertain the number of people registered on the UKCFR who were recorded as discontinuing from ICS in the study period (1 January 2016–30 June 2018). We also ascertained that key variables required for the analysis appear to be reliably recorded.

There were 536 people who discontinued ICS in the study period after at least 90 days of sustained use, before applying the other exclusion criteria (see *Covariates*). ICS start and stop dates appear to have been recorded consistently across the study period. Data on intravenous antibiotic episodes (see *Outcomes*) were also recorded reliably from 2016 onwards with exact dates for the beginning and end of treatment days.

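### The per-protocol censoring model has no stated treatment-arm term: fitted to both arms it weights discontinuers by the wrong process, and fitted by arm within each artificial trial it cannot be estimated reliably

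*Protocol article*

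**What the plan says.** In the protocol article, Main analysis, the prevalent new-user design (PNUD) subsection gives the per-protocol method. People who leave their baseline treatment status are censored. The probability of remaining uncensored is "estimated based on a Cox regression where censoring is the outcome and adjustment is made for the baseline covariates", and these covariates are further described as "the same covariates adjusted for in the PS-based weighting procedure". The sequential trials subsection carries the rule over with one change: "IPCW weights will be derived as specified in the PNUD above, but separately in each artificial trial".

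The Treatment strategies section makes clear that deviation runs both ways: discontinuers may go back on ICS and continuers may stop. Trial spacing is illustrative: "For example, this may entail successive monthly trials within which continuers and new discontinuers are identified". The only count is in Data checks and feasibility analysis: "There were 536 people who discontinued ICS in the study period after at least 90 days of sustained use". That count was taken "before applying the other exclusion criteria", so it is an upper bound.

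The two outcome analyses differ. The PNUD uses a weighted Cox model with treatment as its sole covariate, and a weighted Aalen-Johansen estimator in each group. The sequential design uses a Cox model with treatment and the baseline confounders, followed by standardisation.

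**The concern.** Treatment arm is the outcome of the propensity model, so it cannot be one of that model's covariates. A censoring model that reuses those covariates therefore has no arm term, unless one is specified elsewhere.

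Restarting and stopping are different processes, and one covariate can plausibly act in opposite directions on them. Asthma is the obvious candidate: it could make restarting more likely and stopping less likely. A single model without arm estimates a mixture of the two processes, dominated by the larger group. The natural repair is to fit by arm, but the per-trial rule then leaves too few discontinuers.

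The per-protocol effect is a stated contrast in both designs, and the article says the intention-to-treat effect may be less relevant when people switch. The article also compares the two designs' estimates with each other. Faulty weighting that affects the designs differently could be mistaken for a difference between designs.

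**Working it through.** The plan gives no power or per-trial figure to reproduce. The check starts from its count of 536.

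**Inputs from the article**
- 536 discontinuers, before the other exclusions.
- 1 January 2016 to 30 June 2018, which is 30 months.
- Follow-up of at most 6 months.
- Covariates: counting each listed item once, with time since annual review, gives 19 terms. Splitting home from hospital intravenous antibiotics (+1) and the mucoactive therapies into three (+2) gives 22. Genotype is counted as one term.

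**Assumptions not in the article**
- Stops are spread evenly over the 30 months.
- 10% to 50% of discontinuers restart within 6 months.
- About 1,000 people are in each monthly trial.

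**1. Discontinuers per trial**
- Monthly: 536/30 = 17.9. Quarterly: 536/10 = 53.6.
- If only 50% to 80% of the 536 remain eligible, the monthly figure is 8.9 to 14.3.

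**2. Both arms in one model, no arm term, per monthly trial**
- Continuers' stops in 6 months: about 6 × 17.9 = 107.
- Restarts at 20%: 0.2 × 17.9 = 3.6.
- Share of events that are stops: 107/(107 + 3.6) = 97%. At 50% restart: 107/(107 + 8.9) = 92%.
- Events per term from the stops: 107/19 = 5.6. All 100 simulated Cox fits with 19 covariates were stable, so this model can be fitted.
- Mean 6-month weight given to discontinuers: 1/(1 − 110.6/1000) = 1.12, almost unchanged whatever share restarts. With 1,500 people per trial it would be 1/(1 − 110.6/1500) = 1.08.
- Mean weight needed, 1/(1 − restart share): 1.11, 1.25, 1.43 and 2.00 at 10%, 20%, 30% and 50% restart.
- Suppose a covariate doubles the restart hazard and halves the stop hazard. With a 20% restart share in people without it, the relative weight needed is exp(−ln 0.8) = 1.25. A model driven by stops (10.7% in 6 months) gives exp(0.5 × ln 0.893) = 0.95, which is in the wrong direction.

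**3. Discontinuers only, fitted within each trial**

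| Spacing | Restart share | Restarts | Restarts per term (19 terms) | Stable fits of 100 |
|---|---|---|---|---|
| Monthly | 20% | 3.6 | 0.19 | 0 |
| Monthly | 50% | 8.9 | 0.47 | 0 |
| Quarterly | 20% | 10.7 | 0.56 | 41 |
| Quarterly | 50% | 26.8 | 1.4 | 99 |

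Even if every discontinuer in a monthly trial restarted, there would be 17.9 events for 19 to 22 terms.

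**4. Discontinuers only, pooled over trials**
- 10% restart: 54 events, 2.8 per term. 20%: 107 events, 5.6 per term. 30%: 161 events, 8.5 per term.
- All 100 simulated fits were stable at 20%.

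**5. Size in a one-covariate example**

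All inputs here are assumed: asthma in 30%, 6-month cumulative outcome hazard 0.3 without asthma and 0.6 with it, restart hazard ratio 3 and stop hazard ratio 0.5 for asthma. The outcome analysis is not adjusted for asthma, as in the PNUD.
- True per-protocol risk in discontinuers: 1 − (0.7e^−0.3 + 0.3e^−0.6) = 31.7%.
- At 20% restart: unweighted 31.1%, no-arm weights 31.0%, arm-specific weights 31.7%.
- At 50% restart: unweighted 30.1%, no-arm weights 30.0%.

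The error with no-arm weights is 0.7 points at 20% restart and 1.7 points at 50%. In both cases it is slightly larger than with no weights at all.

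**The case against.** The strongest reply is that the sequential design is largely protected. Its outcome model contains treatment and the same baseline covariates that drive the weights. If that model is correct, covariate-dependent censoring is already handled by conditioning, and weights built only from those covariates and time mainly cost precision. This stands. A reader might infer that the sequential hazard ratio or risk difference is pushed in the wrong direction, but the documents do not support that. The example in step 5 resembles the PNUD estimator, not the sequential one.

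A reader might also infer that the planned model cannot be fitted with about 18 discontinuers per trial. That is not supported either. Read literally, the model includes both arms, and continuers supply enough events. The estimation failure belongs to the arm-specific, per-trial version, which the article does not state.

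Three further points stand in part. Monthly spacing is only an example, and wider spacing eases the problem without removing it. The absence of arm is inferred from the covariate list, and appendix 1, to which the article refers for further analysis detail, may specify fitting by arm. The shift in the example is small beside sampling error: with 536 discontinuers the binomial standard error at 31% is √(0.31 × 0.69/536) = 2.0 points. Still, the main text fixes both the covariate set and the per-trial fit, so this is a stated rule and would need reconciling with any different rule in the appendix.

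**Conclusion.** The concern holds as a dilemma. Without arm, the censoring model can be estimated but describes continuers' stopping, so discontinuers get weights unrelated to their own restarting. With fitting by arm inside each trial, the restart model cannot be estimated reliably at monthly spacing, and at quarterly spacing only if many people restart.

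Bias is to be expected mainly in the PNUD per-protocol hazard ratio and cumulative incidence. In the sequential design the main harm is uninformative or unstable weights and lost precision, provided its outcome model is correctly specified. The numerical effect is modest: under 1 point of 6-month risk in the example at 20% restart. The more telling result is that, under those inputs, the planned weights remove none of the bias they are there to remove.

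The intention-to-treat analyses are unaffected. The sizes rest on the assumed restart share, trial size, even spread of stops and covariate effects. The 17.9 per monthly trial rests on the article's own count and dates and on the even spread.

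**What to change.** In both designs, state that censoring is modelled separately for restarting in discontinuers and for stopping in continuers. An equivalent is one model stratified by arm with arm-by-covariate terms. Fit these models pooled over all artificial trials or exposure sets, with a term for trial or calendar time, and replace the per-trial wording in the sequential subsection. If appendix 1 already specifies fitting by arm, bring the main text into line with it.

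The cost is a change of analysis wording and one added assumption: that covariate effects on deviation are stable over the 30 months. Pooling does not guarantee ample data. At 10% restart there are about 54 restarts, or 2.8 per term, and fewer after exclusions, so a reduced covariate set or penalisation may be needed and should be prespecified. Time-updated medication covariates and weight truncation are optional refinements. The required change does not depend on them, and extra terms would further thin the restart model.
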